## Methods

### Study Setting

This is a two-armed, multicenter, double-blind randomized controlled trial (NCT03034330). Stroke survivors and their primary caregivers (up to n=300) were included and randomized in a 1:1 allocation ratio to a two-tier family-oriented care manager–led intervention group (up to n=150) and a volunteer-led control group (up to n=150). In this study, the research team collaborated with 5 local hospitals in the Hong Kong West Cluster, New Territories East Cluster, and New Territories West Cluster and 3 nongovernmental organizations (NGOs) in the Southern, Shatin, and Tuen Mun districts with varied settings. Three on-site teams established the infrastructure to provide direct rehabilitation and support services to stroke patients. The details of the partnering NGOs are listed in Table 1.

**Table 1 table1:** Details of the study sites.

District	Setting	Services
Southern	District Elderly Community Centre	Providing support services to healthy, vulnerable, and frail older adults living in the community and family caregivers
Shatin	Home Support Team of the Integrated Discharge Support Program for Elderly Patients	Providing postdischarge support services for older adult patients, such as meal delivery, household cleaning, home assessment, and modification
Tuen Mun	Community Rehabilitation Day Centre	Providing both professional and psychosocial rehabilitation services to discharged patients with stroke, neurological, or physical impairments

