### Screening, Randomization, and Intervention Allocation

Stroke survivors and their primary caregivers were first to be identified by physicians in the abovementioned 5 hospitals. Potential dyads were referred to the 3 NGOs using a standardized referral form developed by the research team. Stroke survivors and their primary caregivers were also identified from the pool of existing service users of the 3 NGOs. The care team consisted of trained social workers from the 3 NGOs who performed screening using a standardized screening form that comprised data on demographics, family functioning, caregiving burden, depressive symptoms, and willingness to join. Participants were recruited if they met the inclusion criteria, passed at least one threshold in the areas of family functioning, caregiving burden, or depressive symptoms, and showed a willingness to join.

After recruitment, trained social workers from the 3 NGOs notified the research team to conduct randomization. To avoid bias and to ensure an equal number in each group within each study site, group allocation was determined using computer-generated block randomization with a block size of 4 by using SPSS Statistics (version 23.0, IBM Corp). A member of the research team informed the care managers about the subject code for group allocation. The participants and researchers were blinded to the group assignment. The care managers and volunteers were not blinded to the group assignment, because they needed to know the participants’ group assignment to provide interventions.

Upon randomization, trained care managers were assigned to different cases by the NGOs’ internal control while 2-3 trained volunteers were assigned to the same group depending on their availability and gender. The research team was cautious about the gender of the volunteers; female caregivers may find it difficult to face many male volunteers due to traditional values, while male caregivers may be more willing to receive support from male volunteers.

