Three strategies were adopted to ensure that the intervention and control groups were separated throughout the study. First, both interventions were guided by a standardized protocol conducted by the trained interventionists independently. Second, interventions were home-based, which prevented participants from meeting with each other during the intervention period. Last but not the least, the research team served as a safe guide during the monthly field visit to secure protocol compliance.

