### Control Group

The control group received a volunteer-led psychosocial education for 2-3 months. Care managers did not provide any direct intervention for the participants in the control group. Stroke survivors were not involved in the control group intervention. All participants completed a questionnaire at 3 different time points (Figure 1). A baseline assessment (T0) was conducted by care managers or volunteers before the start of the intervention. The first follow-up (T1) was conducted by a trained research assistant immediately after completion of the intervention, and the second follow-up (T2) was conducted by a trained research assistant at 2 months after completion of the intervention. Time points were chosen to better evaluate the effectiveness of the intervention and to reduce the attrition rate.

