The care managers determined the intensity of the intervention after the initial family needs assessment. The weekly sessions selected out of 22 choices are listed in Table 2. The trained care manager provided the first tier of the intervention, consisting of (1) the family needs assessment (session 1), (2) family support and counseling (sessions 2, 3, 4, 5, 6, and 7), (3) psychological support to caregivers (session 12), and (4) care planning and coordination (session 22). Trained volunteers, supervised by the trained care managers, form the second tier of intervention. They mainly provided in-home services, including (1) psychoeducation (sessions 13, 14, 15, 16, and 17), (2) skill-building (sessions 8, 9, 10, and 11), and (3) social support (sessions 18, 19, 20, and 21). Stroke survivors also took part in up to 4 sessions (sessions 18, 19, 20, and 21) if they agreed and were competent to take part in the intervention. However, the participation of the stroke survivors did not affect their caregivers’ involvement in the study and the intervention. Although the intervention was individualized and tailor-made, the research team provided a standardized protocol to guide the trained care managers as well as the trained volunteers in delivering the intervention. Further, the interventionists recorded the sessions conducted as well as the duration of each session in a service log. Because the collaborating NGOs provided social services or rehabilitation services to stroke survivors, rapport building between care managers and stroke families was ensured. All participating stroke families agreed on the intervention and signed consent forms. Further, care managers built a constant feedback mechanism with the participants, which can ensure participant adherence.

**Table 2 table2:** Domains and themes of the intervention sessions.

Domain	Theme	Interventionist	
		Care Manager	Volunteer
Family Needs Assessment	Project orientation, family needs assessment, and goal setting	✔	
Family Support I	Family conference	✔	
Family Support II	Addressing relationship and caregiving issues of spousal caregiver	✔	
Family Support III	Addressing relationship and caregiving issues of adult-child caregiver	✔	
Family Support IV	Rediscovery of family strengths	✔	
Family Support V	Emotion management	✔	
Family Support VI	Empower stroke survivor	✔	
Skill Building I	Caregiver self-care and relaxation		✔
Skill Building II	Mastering care skills		✔

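### The double-blind label, and the statement that participants and researchers were blinded, are not supported by the procedures the article describes

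*Protocol article*

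**What the plan says.** Under Study Setting the protocol article describes the design in one line: "This is a two-armed, multicenter, double-blind randomized controlled trial". The section Screening, Randomization, and Intervention Allocation then says who was masked: "The participants and researchers were blinded to the group assignment". It also names the exceptions: "The care managers and volunteers were not blinded to the group assignment, because they needed to know the participants’ group assignment to provide interventions".

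The same section says that site social workers notified the research team, which carried out the randomization, and then: "A member of the research team informed the care managers about the subject code for group allocation". Among the measures for keeping the arms apart it lists that "the research team served as a safe guide during the monthly field visit to secure protocol compliance".

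On data collection, the Control Group section says: "A baseline assessment (T0) was conducted by care managers or volunteers before the start of the intervention". It assigns the first and second follow-ups (T1 and T2) to a trained research assistant. Whether that assistant was blinded is covered only by the general word researchers.

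Table 3 and the abstract name two primary outcomes: the Family Role Performance Scale and the Family Assessment Device-General Functioning (FAD-GF) scale.

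**The concern.** Two blanket claims, one about participants and one about researchers, sit beside procedures that do not fit them. Some researchers must know the allocation, because they generate it and pass it on. Participants receive packages that differ in who comes to the home, how often, and whether the stroke survivor takes part.

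This matters because of who does the rating. When the caregiver is both the recipient of the intervention and the source of the primary outcome, protection against performance and reporting bias depends on the caregiver's own masking. A reader or evidence reviewer who takes the label at face value would treat the self-reported result as protected, and would state the conclusion more strongly than the design allows.

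**Working it through.** The plan gives no figure to reproduce here, so the check sets the blinding statements beside the procedures, role by role.

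**1. What the claim covers.** The blinding sentence concerns the group assignment itself. It does not say only that participants were unaware of the hypothesis, or of which arm was experimental.

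**2. Research team.** The team randomizes and a member relays the allocation. For those people the claim that researchers were blinded cannot hold. It could hold for other members, but the sentence makes no distinction.

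**3. Families.** What each arm sees, from the sections Intervention Group, Control Group, Two-Tier Family-Oriented Care Manager–Led Intervention, and Volunteer-Led Psychoeducation:

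| Feature | Intervention | Control |
|---|---|---|
| Who delivers | Social-worker care manager plus volunteers | Volunteers only; no direct intervention by the care manager |
| Home contacts | 6 to 10 sessions | 4 visits |
| Telephone contacts | None described | 2 |
| Content | Tailored, chosen from 22 sessions, including family conference and support | Fixed, not family-based education |
| Stroke survivor | Up to 4 sessions, optional | Not involved |

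Total contacts can coincide (4 + 2 = 6 in control; 6 at the lower end of the intervention). Home contacts cannot, since 6 to 10 against 4 is a difference of 2 to 6. Provider, content and survivor involvement also differ. No procedure is described for masking these features. Home delivery, listed as a way to separate the arms, keeps families from meeting each other. That limits contamination but does not hide from a family what it receives.

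**4. Who rates the primary outcomes.** The Family Role Performance Scale asks participants how often, and how well, they perform family roles. The FAD-GF consists of agree/disagree items on the caregiver's family functioning. Both are caregiver ratings. The Primary Outcome Measures text also names the Care Management Strategies Scale and the Family Caregiver Conflict Scale. These are questionnaires too, so the point does not depend on which list is used.

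**5. Follow-up assessors.** Nothing shows that the T1/T2 research assistants knew the allocation. If they were blinded, interviewer influence is reduced, but the rating remains the caregiver's.

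**6. Baseline (T0) assessors.** Care managers or volunteers collect T0, and these are the two roles declared unblinded. This matters only if T0 came after randomization. Three features point that way:
- the text runs from recruitment to randomization to the assignment of care managers and volunteers;
- baseline assessments feed the needs assessment, which is session 1 of the intervention;
- 264 caregivers were enrolled but 200 participants completed the baseline questionnaire, a gap of 264 − 200 = 64.

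None of these settles it. The article places T0 before the intervention but never before or after randomization, and the flow diagram is not reproduced in the text available.

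**The case against.** The best defence has four parts.

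*Families may not have known their arm.* The control is active, is delivered at home under a standard protocol, and uses volunteers, who also work in the intervention arm. A family that does not know the other arm's content cannot easily tell which arm it is in. A reader might infer from "All participating stroke families agreed on the intervention and signed consent forms" that families were told. That sentence does not say both arms were disclosed, and the consent form is not available. So the documents do not establish that families knew their assignment; this is an inference, though a strong one given the differences in the table. What stands is that blinding of participants is asserted with no procedure behind it.

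*Only one team member need know.* The text says a member relayed a subject code, so the rest of the team could have been masked. That is fair, and it is a reason to limit the claim to those people. A reader might also infer that the monthly visitors saw allocations, since they were securing compliance with two different protocols. The article does not say so.

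*The article already declares care managers and volunteers unblinded.* True, so it does not contradict itself about those roles. Calling the baseline contaminated would go further than the text, because the order of T0 and randomization is not stated.

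*Bias is acknowledged.* The Discussion mentions potential bias in general terms and answers it with standardized training. It does not touch the blinding claim.

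**Conclusion.** The concern holds as a mismatch between the stated blinding and the described procedures. For the staff who randomize and relay allocation, the blanket claim is contradicted by the text. For families, it is unsupported and implausible given openly different packages. The label therefore promises protection that the design does not show for caregiver-rated primary outcomes.

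The baseline limb is conditional on T0 having followed randomization. It should be resolved by stating the order, not presumed.

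No size can be attached. A reader might want to express an assumed reporting bias as a share of a medium effect, or as an inflated false-positive rate. The documents support neither. They give no estimate of such bias. The Sample Size Calculation mentions a medium effect but gives no standardized value, and it derives its 140 per group from readmission or residential admission of 15% against 30%. The consequence is for how strongly the result may be stated.

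**What to change.** Remove the double-blind label and the blanket sentence on participants and researchers, here and in the results report. Replace them with a statement by role:

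- **Care managers and volunteers:** not blinded, as already stated.
- **Team members who randomized or relayed allocation:** not blinded.
- **T1/T2 research assistants:** claim blinding only for those with no part in allocation and no other access to it.
- **Caregivers and survivors:** do not claim blinding to the treatment received. At most, say they were not told which arm was experimental, if that is true.
- **Baseline:** state whether T0 came before or after randomization, and hence whether the person collecting it could know the arm.

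Add to the limitations that the self-reported primary outcomes are open to performance and reporting bias, and word the conclusions accordingly. Masking of the analyst is commonly left to the analysis plan and is not part of this request.

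The change needs no new data or staff, and it can still be made because the article describes the results as yet to be published. The price is that the stated design quality becomes less favourable.

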### Protocol Development

The research team developed a standardized protocol consisting of 3 guidelines, that is, a Care Manager Manual (with 4 chapters), an Intervention Group Protocol for Volunteers (with 13 chapters), and a Control Group Protocol for Volunteers (with 6 chapters) to facilitate the intervention program. The research team provided training to the care managers and volunteers separately. First, we conducted a 4-day (32-hour) training session for 9 care managers (3 from each NGO) in 2016, covering the topics of the medical aspects of stroke, the intervention and assessment framework, care management, family therapy, coping with stress, problem-solving, stroke rehabilitation, and family intervention skills. Second, we provided a 5-day (40-hour) training workshop to 46 volunteers recruited by the 3 NGOs, focusing on the impact of stroke, psychoeducation, in-home exercise training, personal care techniques, counseling skills, swallowing and communications, intervention assessment, and code of practice. The number of volunteers recruited was estimated by care managers of the 3 NGOs based on the intervention protocol and resource management.

### Intervention Group

Both groups followed a standardized protocol designed by the research team. The intervention group received a two-tier family-oriented care manager–led intervention consisting of a trained social worker (care manager) and trained volunteers for 2-3 months.

### Control Group

The control group received a volunteer-led psychosocial education for 2-3 months. Care managers did not provide any direct intervention for the participants in the control group. Stroke survivors were not involved in the control group intervention. All participants completed a questionnaire at 3 different time points (Figure 1). A baseline assessment (T0) was conducted by care managers or volunteers before the start of the intervention. The first follow-up (T1) was conducted by a trained research assistant immediately after completion of the intervention, and the second follow-up (T2) was conducted by a trained research assistant at 2 months after completion of the intervention. Time points were chosen to better evaluate the effectiveness of the intervention and to reduce the attrition rate.

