#### Two-Tier Family-Oriented Care Manager–Led Intervention

The intervention was individualized and tailor-made according to the caregivers’ needs assessment results. Care managers conducted an initial family needs assessment with caregivers to determine the care plan. Baseline assessments and a family genogram were used to assess caregivers’ needs. Measures covered demographic information, stroke knowledge, care management strategies, family conflicts, family functioning, social network, caregiver burden, physical and mental health, and depressive mood. The intervention lasted for 2-3 months with 6-10 weekly sessions at the homes of the caregivers or stroke survivors. Each session lasted for 60-90 minutes. The flexibility in the duration was provided based on the consideration that some participating families were more willing to share and discuss in detail, as evidenced in the pilot experiences. The research team visited each study site every 4 weeks to ensure project progress and held a full team meeting with the 3 NGOs every 12 weeks to share good practices.

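### Baseline outcomes are taken by unblinded interventionists, apparently after allocation, which puts the change-from-baseline comparison at risk of bias and leaves the double-blind label too broad

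*Protocol article*

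**What the plan says.** All places are in the protocol article.

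- **Who takes T0** (Control Group): "A baseline assessment (T0) was conducted by care managers or volunteers before the start of the intervention".
- **Who takes follow-up** (same section): "The first follow-up (T1) was conducted by a trained research assistant immediately after completion of the intervention". T2, two months later, is likewise taken by a research assistant.
- **Who is unblinded** (Screening, Randomization, and Intervention Allocation): "The care managers and volunteers were not blinded to the group assignment". The reason given is that they had to deliver the interventions.
- **Who is blinded** (same section): "The participants and researchers were blinded to the group assignment".
- **Order of events** (same section): screening, recruitment, randomisation, then staffing of the case: "Upon randomization, trained care managers were assigned to different cases". No T0 step is placed before allocation.
- **Use of baseline data in the intervention arm** (Two-Tier Family-Oriented Care Manager–Led Intervention): "Baseline assessments and a family genogram were used to assess". What is assessed there is the caregiver's needs, and the care manager's needs assessment sets the care plan.
- **Control arm** (Volunteer-Led Psychoeducation): volunteers deliver, and care managers supervise them without intervening directly.
- **Analysis** (Statistical Analysis): a multi-factor analysis of variance or general linear model compares the arms on change in each outcome over T0, T1 and T2.
- **Label** (Study Setting): "This is a two-armed, multicenter, double-blind randomized controlled trial".

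**The concern.** The outcomes are questionnaire scores for family functioning, conflict, burden and mood. Answers to such questions can depend on who asks and for what purpose. T0 anchors every change estimate, and it is taken by people who deliver the interventions and know the arm.

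In the intervention arm T0 also serves care planning. The needs assessment covers family functioning, conflict, care management strategies, burden and depressive mood, which overlap heavily with the outcomes in Table 3. No such use of T0 is described for the control arm. If this moves T0 answers in one arm only, the movement enters the change contrast in full and a baseline-adjusted contrast in part. It could create an apparent effect or hide a real one.

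The double-blind label would lead a reader to assume that this route to bias is closed.

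**Working it through.** **What the text settles**

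| Question | Answer in the article |
|---|---|
| Are T0 assessors interventionists? | Yes, stated |
| Are care managers and volunteers unblinded? | Yes, stated |
| Do assessors change between T0 and T1/T2? | Yes, stated |
| Does T0 enter the main comparison? | Yes, stated |
| Does T0 follow randomisation? | Natural reading; the text says only that T0 precedes the intervention |
| Does assessor type or setting differ by arm? | Likely; not stated |

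The article gives no figure on this point to reproduce, and no value for an assessor effect. What follows shows sensitivity to a shift and does not estimate one.

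**Inputs**

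- Two-sided α = 0.05 (Statistical Analysis).
- n = 100 per arm: the 200 participants with baseline questionnaires (Results), assumed to be split equally.
- Correlation ρ between T0 and follow-up: assumed 0.5, with 0.7 as an alternative.
- Shift s at T0 in one arm only, in SD units: assumed 0 to 0.3.
- No true treatment effect; unit SD at each time point; normal approximation.

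**Formulas**

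- Change score: bias in size = s; SE = √(2(1−ρ)) × √(2/n).
- T0 as covariate: bias in size = ρs; SE = √(1−ρ²) × √(2/n).
- Follow-up score without T0: bias = 0.
- Type I error = 1 − Φ(1.96 − bias/SE) + Φ(−1.96 − bias/SE).

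**At ρ = 0.5, n = 100**

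√(2/100) = 0.1414. The change-score SE is 1 × 0.1414 = 0.1414. The covariate-adjusted SE is √0.75 × 0.1414 = 0.1225.

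| s (SD) | Change: bias/SE | Type I error | Adjusted: bias/SE | Type I error |
|---|---|---|---|---|
| 0 | 0 | 0.050 | 0 | 0.050 |
| 0.1 | 0.1/0.1414 = 0.71 | 0.109 | 0.05/0.1225 = 0.41 | 0.069 |
| 0.2 | 0.2/0.1414 = 1.41 | 0.293 | 0.10/0.1225 = 0.82 | 0.129 |
| 0.3 | 0.3/0.1414 = 2.12 | 0.564 | 0.15/0.1225 = 1.22 | 0.232 |

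At ρ = 0.7, shifts of 0.1, 0.2 and 0.3 SD give 0.150, 0.447 and 0.782 for change scores, and 0.107, 0.283 and 0.548 with adjustment.

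**What cancels.** Suppose moving from interventionists to research assistants shifts answers by the same amount c in both arms. The between-arm contrast of changes then carries c − c = 0, and type I error stays at 0.05. Only a difference between the arms in T0 conditions matters.

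**Precision without T0.** At ρ = 0.5 the outcome variance is 1 − 0.5² = 0.75 with T0 as covariate and at most 1.0 without it. The loss is up to 1 − 0.75/1.0 = 25% of effective sample size. Against plain change scores at ρ = 0.5, whose variance is 2(1 − 0.5) = 1.0, there is no loss.

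**The case against.** The best defence is that the damaging premises are inferred.

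- **Assessor type by arm.** A reader might conclude that care managers took T0 in the intervention arm and volunteers in the control arm. The article ties neither group to an arm. Assessing is not intervening, care managers supervise the control volunteers, and volunteers work in both arms. Both types assessing in both arms is compatible with the text.
- **Order.** T0 after randomisation is not explicit. The flow diagram (Figure 1) was not available for this review and may settle it. If T0 came first, assessors could not have known the allocation.
- **Missing baselines.** A reader might take the 264 − 200 = 64 enrolled caregivers without baseline questionnaires as lost after allocation. The Results section does not say when or why those baselines are missing, so this cannot be claimed.
- **The label.** Calling double-blind untrue goes too far. The article names participants and researchers as blinded and openly says who is not, and why.
- **Replacing the primary analysis.** The screening scores are a four-item burden score, a two-item depression score and four conflict items. All served as entry thresholds, and none is a primary outcome in Table 3. Rebuilding the primary analysis on them after data collection would be hard to justify.

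All of this stands, and it limits the point to a risk of bias. It does not remove the stated facts that unblinded interventionists supply T0 and that T0 enters the main comparison.

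**Conclusion.** The point holds as a risk of bias. Unblinded interventionists take T0, apparently after allocation; research assistants take T1 and T2; and the main contrast uses change from T0. Bias arises only if T0 conditions differ by arm. The described use of baseline data for care planning in the intervention arm, and the absence of direct care-manager intervention in the control arm, make that likely, but the article does not state it. Size and direction are unknown.

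The percentages rest wholly on an assumed shift, an assumed correlation and an assumed equal split. They show that a modest arm-specific shift would matter and that adjusting for T0 would only partly remove it. They do not show that the trial's results are biased.

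The double-blind label is misleading because it covers neither delivery nor, on the natural reading, baseline assessment. Whether the blinded researchers include the T1 and T2 research assistants needs confirming.

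**What to change.** 1. Keep the planned analysis. Add a sensitivity analysis, fixed in writing before the arms are compared, of the arm difference in the research-assistant-collected T1 and T2 scores without T0, adjusted for site and the pre-randomisation screening scores for family functioning, burden and depressive symptoms.
2. Temper the conclusion if the two analyses disagree.
3. Tabulate T0 scores by arm and assessor type.
4. State whether T0 came before or after randomisation, and who took it in each arm.
5. Replace double-blind with blinding by role: care managers, volunteers and, unless T0 preceded allocation, T0 assessors unblinded; participants and researchers stated as blinded; T1 and T2 assessors to be confirmed.

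No new outcome data are needed; the assessor for each T0 must be taken from study records. The cost is precision in the added analysis: at a correlation of 0.5, up to about 25% of effective sample size compared with a T0-adjusted model, less whatever the screening scores recover. At a correlation of 0.7 the upper limit is larger: 0.7² = 49%. A non-significant result there is therefore not evidence against the main result. Compare the estimates and their intervals.
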